### Interventions

Following selection and attainment of informed consent, all participants will be randomly assigned to either the PREVENA therapy group or conventional dressings group with a 1:1 allocation ratio via stratified randomisation. Participants will be stratified by their baseline comorbidity state and will be stratified into one of the three groups, namely:i)No diabetes nor immunosuppressant useii)Diabetic patients (both insulin, non-insulin dependent, type one or type two)iii)Use of immunosuppressants

Following stratification, participants will be systematically randomized in a 1:1 allocation ratio into either the PREVENA group or the conventional dressing group. The conventional dressings that are used in the study will be non-antimicrobial, standard surgical dressing. On the day of elective admission, the relevant primary or co-investigators will perform this randomisation by picking one of the sealed envelopes containing the assignment. There will be equal proportion of assignments to either group (PREVENA and conventional dressings) to achieve a 1:1 allocation ratio. The conventional dressings that are used in the study will be non-antimicrobial, standard adherent surgical dressing. Due to the nature of the intervention, neither the participants nor the staff can be blinded to allocation. Prophylactic antibiotics will be administered following reversal surgeries as per local guidelines. Initial dose will be administered during induction of the surgeries, followed by three more doses administered post-operatively. Wound closure will be performed in a standardized manner, and the randomized dressing will be applied immediately after wound closure. The PREVENA dressings will be left in situ for 7 days at which point the wound will be inspected for any evidence of SSI. Wound swabs will be performed for culture and sensitivity for any incidence or suspicion of SSI.

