### Outcomes

The primary outcome of PRIC Study is to measure the incidence of investigator assessed SSI within 30 days following reversal of ileostomy or colostomy (confirmed with culture and sensitivity microbial growths). The secondary outcomes are to assess patient satisfaction and experience with either dressing via a visual analogue score (VAS), to measure the time to wound healing and to evaluate wound healing during routine OPD visits through taking photographs and VAS rating by our plastic consultant colleagues.

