## Data collection and management

SSI is assessed using the definition criteria established by the ‘United States Centers for Disease Control and Prevention’ [20]. Post-operatively, the study investigators will assess for any evidence of SSI. Following discharge from the study sites, PHN will routinely carry out home support services including wound assessment and wound care for all participants who have underwent reversal surgery. Should any concerns regarding SSI arise, patients will be referred back to study sites and be reassessed for wound SSI by study investigators. At this point SSI will be confirmed with culture and sensitivity microbial growths. If there are no such concerns of SSI during the house visits, all participants will be routinely reviewed by study investigators for any signs of SSI during their routine OPD visits. The follow-up OPD visits will typically take place approximately 30 days following discharge from the study sites. To measure the time to wound healing, the investigators will liaise with the PHN to gather the relevant data on the time to wound healing, which is calculated from the day of reversal surgery to the day of last PHN home visit.

To assess patient satisfaction, the investigators will be applying a visual analogue scale (VAS) as the measurement instrument, and patient participants will be invited to complete this during OPD visits. The investigators will also take photographs of the surgical site of reversals during routine OPD visits, and these photographs will be blinded to assess for wound healing. Participant retention is strongly promoted through strict scheduling of follow-up appointments.

Data will be collected at both study sites, SJH and TUH, using hospital network computer. They will be password protected and stored in an encrypted folder. To safeguard confidentiality, data will be pseudo-anonymised immediately at the point of collection, and the key code that links the data to patients will be a hard-copy document kept in a secure cabinet on the study site and will be irrevocably destroyed once the study period has been completed. All reports used by the data coordinating centre will be prepared in a manner such that no individual subject can be identified. All data controllers have completed the General Data Protection Regulation (GDPR) training and have experience in collecting and handling patient data from previous studies.

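### Allocation is drawn on admission day although the arm is needed only after closure, and the primary SSI outcome stays with unblinded investigators although later assessments could be blinded: an avoidable risk of bias

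*Protocol article*

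**What the plan says.** All references are to the protocol article.

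- **Allocation (Interventions).** On the day of admission, "the relevant primary or co-investigators will perform this randomisation by picking one of the sealed envelopes". The hour, the moment of opening and who then learns the arm are not stated.
- **When the arm is needed (Interventions).** "Wound closure will be performed in a standardized manner", and "the randomized dressing will be applied immediately after wound closure".
- **Blinding (Interventions).** The article states that "neither the participants nor the staff can be blinded to allocation".
- **Dressing period (Interventions).** "The PREVENA dressings will be left in situ for 7 days at which point the wound will be inspected for any evidence of SSI". Swabs are taken when SSI is present or suspected.
- **Primary outcome (Outcomes; Data collection and management).** The outcome is "investigator assessed SSI within 30 days", using CDC criteria and confirmed by culture. Study investigators assess after surgery, when a public health nurse refers a patient back, and at the outpatient visit.
- **Blinding that is planned (Data collection and management).** For the outpatient wound pictures, "these photographs will be blinded to assess for wound healing". Wound healing is a secondary outcome.

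**The concern.** Two choices open the trial to more bias than an unblindable dressing requires.

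**Timing of allocation.** Nothing in the operation depends on the arm until closure is finished. Drawing the envelope at admission creates an interval in which the arm can be known while the case can still be cancelled or the patient withdrawn, and while the wound is being prepared and closed.

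**Outcome assessment.** The statement that staff cannot be blinded is right for those who apply and manage the dressing. It is too broad for someone who examines the wound after the dressing has gone. As planned, the investigator who may know the arm decides both whether SSI is present and whether the wound looks suspicious enough to swab. A wound that is never suspected is never cultured, so it cannot become a confirmed SSI.

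The Conclusion of the Abstract says the trial will inform whether routine NPWT becomes standard of care. The primary comparison should therefore not be open to differential ascertainment that could have been prevented.

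**Working it through.** **1. Place the steps in time.**

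| Step | When | Must the person know the arm? |
|---|---|---|
| Consent and recruitment | Outpatient clinic, before admission | No |
| Envelope drawn | Day of admission | No |
| Surgery and closure | After admission | No |
| Dressing applied | Immediately after closure | Yes |
| PREVENA in place | To day 7 | Arm is visible |
| SSI assessment after removal (referral back, outpatient visit) | Rest of follow-up | No |

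The arm is drawn one step too early, and the last row could be blinded.

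**2. Reproduce the plan's own figure.** Inputs from Sample size: 25% and 10%, α = 0.05, power 0.80. The two-sided test is from Data analysis. With pooled p̄ = 0.175:

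n = [1.960·√(2·0.175·0.825) + 0.842·√(0.25·0.75 + 0.10·0.90)]² / 0.15²

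= (1.960·0.5374 + 0.842·0.5268)² / 0.0225 = 99.5, so 100 per arm, as stated. With 10% dropout, 200/0.90 = 222.2, which matches the stated figure of about 222. The point here does not touch these numbers.

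**3. Illustrate what differential recording would do.** Suppose there is no true effect and the SSI rate is p in both arms, but a fraction m of SSIs in the NPWT arm goes unrecorded. The test then compares p with p(1 − m). The values of m are assumptions; the article gives none.

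Worked line by normal approximation, p = 0.25 and m = 0.20, so 0.25 against 0.20 with 100 per arm:

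- SE under the null = √(2·0.225·0.775/100) = 0.05906
- SE under the alternative = √[(0.25·0.75 + 0.20·0.80)/100] = 0.05895
- Upper tail: Φ[(0.05 − 1.96·0.05906)/0.05895] = Φ(−1.115) = 0.132
- Lower tail: Φ[(−0.05 − 1.96·0.05906)/0.05895] = Φ(−2.812) = 0.002
- Total 0.135

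Exact rejection probabilities of the Pearson chi-squared test, 100 per arm (sum of the two binomial distributions over the rejection region):

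| Unrecorded in NPWT arm | p = 25% | p = 10% |
|---|---|---|
| 0% | 4.9% | 5.2% |
| 5% | 5.4% | 5.4% |
| 10% | 7.0% | 5.9% |
| 20% | 13.5% | 8.0% |
| 30% | 25.6% | 12.0% |

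At 34%, the control rate of one earlier trial cited in the Discussion, 10%, 20% and 30% give 8.2%, 18.3% and 35.9%. Small under-recording does little harm; 20% or more matters at the planned control rate.

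**The case against.** The protocol has real safeguards, and several stronger readings go beyond it.

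- **A reader might infer that the arm is revealed before surgery.** The article does not say so. It gives the day of the draw, not the moment of opening, and does not say that the surgeon learns the arm. What stands is that nothing in the stated procedure prevents it.
- **A reader might infer that picking an envelope means there is no fixed or concealed sequence.** Numbering, opacity and sequence generation are details an article may leave to the full protocol. Their absence is not a finding.
- **Selection is limited.** Recruitment and consent precede the draw, so sealed envelopes protect enrolment. The remaining exposure is cancellation or withdrawal after allocation, and no section says this would depend on the arm.
- **Performance is limited.** Closure is standardized. This reduces the room for differences but does not remove it.
- **Detection is limited.** CDC criteria and culture restrain over-calling. They do not cure under-detection, because an unblinded suspicion triggers the swab. First suspicion at home also passes through public health nurses, whom a blinded hospital assessor does not reach.
- **Blinding cannot be complete.** SSIs arising with the dressing on are judged with the arm visible, and patients can disclose their arm later.
- **The illustration is hypothetical.** No document supports any particular under-recording rate, or that errors would run in favour of NPWT.

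These objections narrow the point but leave its core: the draw is earlier than it need be, and the primary outcome has no blinded assessor where one is feasible.

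**Conclusion.** The concern holds as an avoidable risk of bias. It is not a demonstration that bias enters or that it favours NPWT. Two features support it: allocation on admission day when the arm is needed only after closure, and a blanket statement on blinding that leaves the primary outcome with unblinded investigators while a secondary outcome is assessed blind.

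Its size depends on assumptions. With no true effect, 100 per arm and 5% to 30% one-sided under-recording, the two-sided type I error lies between 5.4% and 25.6% at a 25% SSI rate, and between 5.4% and 12.0% at 10%. With equal recording in both arms it stays near 5%. The change is worth making because it is cheap and the primary result depends on it.

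**What to change.** 1. **Allocation.** Open the next sealed envelope in the participant's stratum only after skin closure is complete.
2. **Assessment after dressing removal.** Have the scheduled outpatient visit and any referral back assessed for SSI by an existing investigator who did not operate and is not told the arm. The same person decides whether the wound meets the protocol's existing condition for a swab; the condition itself is unchanged.
3. **Wording.** Limit the statement that blinding is impossible to participants and treating staff.
4. **Acknowledge what remains.** State that SSIs arising while the dressing is on, and disclosure by patients, are not covered.

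Blinded review of photographs from already suspected cases should not replace this as the primary classification. It sees only wounds that an open assessor has flagged, so it cannot recover missed SSIs.

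Cost: a short delay in theatre and a rota change among existing investigators. The sample size stays at 100 per arm, about 222 in total.

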### Outcomes

The primary outcome of PRIC Study is to measure the incidence of investigator assessed SSI within 30 days following reversal of ileostomy or colostomy (confirmed with culture and sensitivity microbial growths). The secondary outcomes are to assess patient satisfaction and experience with either dressing via a visual analogue score (VAS), to measure the time to wound healing and to evaluate wound healing during routine OPD visits through taking photographs and VAS rating by our plastic consultant colleagues.

### Sample size

Based on published literature, we hypothesize a 60% reduction in SSI rates following the routine use of NPWT (25 to 10% at closure site). The study will be a randomized, controlled, open-label trial with two parallel arms comparing standard and routine NPWT applied immediately after reversal of ileostomy or colostomy. The sample size required to achieve a power of 1-β = 0.80 and at the level α = 0.05 under these assumptions (including a margin error with application failure, saturation and patient non-compliance) amounts to 100 patients needed for each arm; thus 2 × 100 = 200 participants are required. We incorporate a 10% dropout rate in our sample size calculation, and this would inflate the sample size to approximately 222 participants.

## Data collection and management

SSI is assessed using the definition criteria established by the ‘United States Centers for Disease Control and Prevention’ [20]. Post-operatively, the study investigators will assess for any evidence of SSI. Following discharge from the study sites, PHN will routinely carry out home support services including wound assessment and wound care for all participants who have underwent reversal surgery. Should any concerns regarding SSI arise, patients will be referred back to study sites and be reassessed for wound SSI by study investigators. At this point SSI will be confirmed with culture and sensitivity microbial growths. If there are no such concerns of SSI during the house visits, all participants will be routinely reviewed by study investigators for any signs of SSI during their routine OPD visits. The follow-up OPD visits will typically take place approximately 30 days following discharge from the study sites. To measure the time to wound healing, the investigators will liaise with the PHN to gather the relevant data on the time to wound healing, which is calculated from the day of reversal surgery to the day of last PHN home visit.

To assess patient satisfaction, the investigators will be applying a visual analogue scale (VAS) as the measurement instrument, and patient participants will be invited to complete this during OPD visits. The investigators will also take photographs of the surgical site of reversals during routine OPD visits, and these photographs will be blinded to assess for wound healing. Participant retention is strongly promoted through strict scheduling of follow-up appointments.

Data will be collected at both study sites, SJH and TUH, using hospital network computer. They will be password protected and stored in an encrypted folder. To safeguard confidentiality, data will be pseudo-anonymised immediately at the point of collection, and the key code that links the data to patients will be a hard-copy document kept in a secure cabinet on the study site and will be irrevocably destroyed once the study period has been completed. All reports used by the data coordinating centre will be prepared in a manner such that no individual subject can be identified. All data controllers have completed the General Data Protection Regulation (GDPR) training and have experience in collecting and handling patient data from previous studies.

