### Study setting and design

This study is designed as a randomized, controlled, open-label, multi-centre superiority trial with two parallel groups with a primary endpoint of measuring SSI incidence within 30 days of reversal of ileostomy or colostomy. The trial will be conducted at two centres located in Dublin, Ireland: St James’s Hospital and Tallaght University Hospital.

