### Data analysis

Data analysis, processing and calculation of inferential statistics will be performed primarily using SPSS software. In relation to primary endpoint analysis, which assesses the presence of SSI within 30 days following reversal surgeries, a Chi-squared test will be used to compare the SSI incidence rates between the two randomized groups (PREVENA vs conventional surgical dressings). The time to wound healing, patient experience and satisfaction and the degree of wound healing and wound aesthetics will be presented as secondary outcomes. A t-Test will be applied to compare the time to wound healing between the randomized groups as appropriate. Similarly, t-Test will be applied to compare the level of satisfaction between patients of the randomized groups. All outcome measures will be presented with 95% confidence intervals and two-sided test *p* values.

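### The 30-day SSI endpoint runs from surgery, but the routine investigator review is timed from discharge and so nominally falls after the window has closed

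*Protocol article*

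**What the plan says.** The endpoint is counted from surgery wherever the article defines it. Study setting and design gives a "primary endpoint of measuring SSI incidence within 30 days of reversal of ileostomy or colostomy". Outcomes gives the "incidence of investigator assessed SSI within 30 days following reversal of ileostomy or colostomy" and adds that culture must confirm the infection. Data analysis applies the chi-squared test to the "presence of SSI within 30 days following reversal surgeries". The Abstract uses the same origin.

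Data collection and management describes how SSI is found. Investigators assess patients post-operatively, and the Abstract adds a wound examination on day seven. After discharge, public health nurses assess the wound at home: "Should any concerns regarding SSI arise, patients will be referred back to study sites and be reassessed for wound SSI by study investigators". If the nurse has no such concern, "all participants will be routinely reviewed by study investigators for any signs of SSI during their routine OPD visits". The timing of that review is then given: "The follow-up OPD visits will typically take place approximately 30 days following discharge from the study sites".

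The Interventions section states that neither participants nor staff can be blinded. Data collection and management blinds the photographs used to judge wound healing, but describes no blinding of the SSI assessment.

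**The concern.** The endpoint and the visit have different starting points, and the gap between them is the length of hospital stay. The visit matters because the endpoint requires an investigator's assessment, and this is the routine investigator review for every participant who was not referred back by a nurse.

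Two kinds of error can follow. An infection that begins after day 30 may be found at the visit and counted as an event. An infection that begins and settles inside the window without alarming the nurse may leave nothing to see or swab. The article states no rule for an SSI first found after day 30. Investigators who know the allocation would therefore have to judge, after the fact, whether it began in time. That is an avoidable opening for differential classification of the trial's only primary endpoint.

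**Working it through.** **1. Time origins side by side.**

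| Item | Counted from | Nominal length | Section |
|---|---|---|---|
| Primary endpoint | Reversal surgery | 30 days | Abstract; Study setting and design; Outcomes; Data analysis |
| Routine investigator SSI review | Discharge | About 30 days | Data collection and management |

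**2. When the review falls.** Let L be the stay in days from surgery to discharge. Review day after surgery = L + 30, and days past the close of the window = (L + 30) − 30 = L. The article does not give L, so the values below are assumptions.

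| Assumed L | Review on post-operative day | Days after window closes |
|---|---|---|
| 2 | 32 | 2 |
| 3 | 33 | 3 |
| 5 | 35 | 5 |
| 7 | 37 | 7 |
| 10 | 40 | 10 |

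Any L above zero puts the nominal review outside the window, and its distance from surgery varies day for day with the stay.

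**3. Which investigator assessments the text places inside the window.** There are three: the post-operative assessment, the day-seven examination, and reassessment after a nurse's referral. The third happens only if the nurse is concerned. For a participant without nurse concern, the text fixes no investigator assessment between day 7 and a date nominally past day 30.

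**4. What the late review can establish.**
- *SSI began by day 30 and is still present:* it is found and can be cultured, but the positive swab dates from the visit. Onset has to be reconstructed.
- *SSI began and resolved by day 30 without nurse concern:* culture is no longer possible, so the confirmation in Outcomes cannot be met.
- *SSI began after day 30:* it is found and cultured, and without an onset date it looks the same as the first case.

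**5. Sample size, for context.** The inputs in Sample size are 25% against 10%, α = 0.05 and power 0.80; Data analysis specifies two-sided tests. The pooled-variance formula without continuity correction gives

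n per arm = [1.960·√(2 × 0.175 × 0.825) + 0.842·√(0.25 × 0.75 + 0.10 × 0.90)]² / 0.15² = 100 after rounding up.

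This reproduces the stated 100, with power 0.802 at that number. The timing mismatch does not make the calculation wrong. The table shows how little reserve there is, using purely assumed error rates that are equal in both arms, at 100 per arm.

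| Assumption | Rates compared | Power |
|---|---|---|
| No error | 25% v 10% | 0.80 |
| 2 points of late SSI added to each arm | 27% v 12% | 0.77 |
| 5 points of late SSI added to each arm | 30% v 15% | 0.72 |
| 10% of SSI missed in each arm | 22.5% v 9% | 0.75 |
| 20% of SSI missed in each arm | 20% v 8% | 0.69 |

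The article supplies none of these error rates. The table does not estimate what will happen.

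**The case against.** The best defence is that SSI within the window is already looked for: post-operatively, on day seven, and by nurses who visit all participants at home and refer any concern to an investigator for assessment and culture. On this view the clinic visit is only a final check on people who seemed well. A last look after day 30 is also no fault in itself, since a visit before day 30 cannot observe the whole window. Onset-date fields and counting rules may sit in the full protocol or analysis plan.

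Much of this stands, and it rules out several stronger readings that a reader might infer:

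- *The review always falls after day 30.* The sentence is qualified by *typically* and *approximately*, so after a short stay a visit could fall on or before day 30. Nothing requires that, however. The article also speaks of visits and appointments in the plural. That may simply run across participants, but it means a single clinic visit per patient is not proven.
- *The endpoint window changes with hospital stay.* It does not. It is fixed at 30 days; only the date of the last routine investigator look varies.
- *The trial does not measure 30-day SSI.* The nurse and referral route contradicts this.
- *Longer stays give one arm more chance of an event.* The article has no data on stay by arm, and a patient kept in because of an SSI already has the event.
- *The extra days measure the bias.* They come from assumed stays and do not show how many SSI would be misclassified.

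The defence does not remove the mismatch. Referral depends on a nurse's concern, and the article gives no schedule or criteria for the nurse visits. The visit timing is stated in the text, so this is a conflict and not a detail left out. A later counting rule could sort the late findings, but it could not recover assessments that were never made inside the window.

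**Conclusion.** The point holds in a limited form. The endpoint is timed from surgery and the routine investigator review from discharge. For any inpatient stay, the nominal review comes after the window closes by about the length of stay: day 32 to 40 if stays run from 2 to 10 days, which is an assumption. For participants without nurse concern, in-window ascertainment by an investigator is weakened, and the side of day 30 on which a late-found SSI belongs is left to unblinded judgement. The effect on the SSI rates, the treatment comparison and power cannot be quantified from the article, and no direction of bias is shown. The planned sample size is unaffected. Because the problem bears on the only primary endpoint and is cheap to remove, it should be corrected.

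**What to change.** - Anchor the final SSI review to surgery in both arms, on or shortly after post-operative day 30, for example day 30 to 33. The interval should not open before day 30, because an earlier visit leaves the end of the window unobserved.
- Record the onset date of every SSI, using the nurse's records where available.
- State that the primary endpoint counts only SSI with onset by day 30 after surgery, and report later onsets separately.
- Align the timing sentence in Data collection and management with the endpoint definition in the other sections.

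The cost is moving an existing visit and adding one date field. Onset of an SSI first seen at the review will still need some reconstruction, but the review will be at most a few days past the window and the same for every patient regardless of stay.

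### Time to wound healing ends at the last nurse home visit whether or not the wound has closed, and the t-test cannot handle wounds still open

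*Protocol article*

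**What the plan says.** Under Data collection and management, the investigators obtain healing data from the public health nurses (PHN): "the investigators will liaise with the PHN to gather the relevant data on the time to wound healing". The interval is "calculated from the day of reversal surgery to the day of last PHN home visit".

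The same section describes the home visits as a routine service: "PHN will routinely carry out home support services including wound assessment and wound care for all participants". It gives no criterion for a healed wound and no rule for when visits end. On suspected infection it says: "Should any concerns regarding SSI arise, patients will be referred back to study sites and be reassessed for wound SSI by study investigators". It does not say whether home visits then stop, pause or resume. Patients without such concerns are seen by the investigators in clinic: "The follow-up OPD visits will typically take place approximately 30 days following discharge from the study sites".

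Data analysis names the method: "A t-Test will be applied to compare the time to wound healing between the randomized groups as appropriate". No censoring rule accompanies it.

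A shorter time to healing is the first secondary objective under Objectives. Under Outcomes it comes after patient satisfaction.

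**The concern.** The end of the interval is the date of a service contact, while the quantity of interest is the date of a biological event. The two agree only if the last visit is the one at which closure is seen. Since no healed status is required, every patient with a home visit gets a complete time, including any patient whose wound was still open. The t-test then averages these times as if all wounds had closed.

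This would matter less if it affected both arms alike. However, the one route out of home care that the article describes is referral for suspected SSI, and SSI is the outcome on which the arms are expected to differ. If some referred patients have no later home visit, slow-healing wounds get short recorded times, and more of them would be in the conventional-dressing arm. That would shrink a real benefit of negative pressure wound therapy (NPWT) on healing. The Discussion says that the healing results may be used in later cost-benefit studies, so an error here could carry forward.

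**Working it through.** The article gives no expected healing time, spread or target difference, so there is no figure of the plan's own to reproduce. The sample size of 100 per arm is for the SSI endpoint and has no bearing here.

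**Inputs**
- From the Sample size section: SSI in 25% (conventional) and 10% (NPWT).
- Assumed, because the article gives no values: closure at 20 days without SSI and 45 days with SSI, the same in both arms; last home visit at day 12 when visits end early; for everyone else the last visit falls on the day of closure.
- Varied: r, the share of SSI patients whose home visits end early, taken as equal in both arms.

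**Formula**

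Mean recorded time in an arm with SSI proportion p:

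(1 − p) × 20 + p × [(1 − r) × 45 + r × 12]

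Conventional minus NPWT (positive favours NPWT):

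(0.25 − 0.10) × [(45 − 33r) − 20] = 0.15 × (25 − 33r)

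**Results**

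| r | Conventional (days) | NPWT (days) | Difference (days) |
|---|---|---|---|
| 0 (true values) | 26.25 | 22.50 | 3.75 |
| 0.5 | 22.125 | 20.85 | 1.275 |
| 1 | 18.0 | 19.2 | −1.2 |

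The sign changes where 25 − 33r = 0, at r = 25/33, or about 0.76.

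**Sensitivity to the assumed days**

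With closure at 21 and 45 days, the true difference is 0.15 × 24 = 3.6 days.
- Early last visit at day 10: 0.15 × (24 − 35r). This gives 0.975 days at r = 0.5 and −1.65 at r = 1; the sign changes at 24/35, about 0.69.
- Early last visit at day 14: 0.15 × (24 − 31r). This gives −1.05 days at r = 1; the sign changes at 24/31, about 0.77.

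A simulation of the day-10 case used 100 patients per arm and 4,000 repeats, with assumed standard deviations of 6 days (closure without SSI), 10 days (closure with SSI) and 3 days (referral). The t-test was significant in about 62% of trials at r = 0, 31% at r = 0.25 and 11% at r = 0.5.

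**The other direction**

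Suppose no visits end early and infected wounds instead get visits for e days beyond closure. The recorded difference is then 0.15 × (25 + e), so each extra day adds 0.15 days in favour of NPWT.

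**The case against.** The strongest reply is that the article never says home visits stop on referral, readmission or handover to clinic. Home wound care is for all participants and the clock stops at the last visit, so a patient who returns to home care after reassessment gets a later date. If nurses visit until closure, the last visit is a sensible proxy. This stands: early recording of infected patients is a possibility, not something the article describes. So does the related point that the direction of bias is not established, since extra nursing of infected wounds would lengthen their recorded times.

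A reader might infer that the rule reverses the treatment effect. The documents do not support that. Reversal needs roughly 70% to 77% or more of SSI patients to have no further home visit, and it rests on assumed healing times.

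A reader might also argue that the 7 days under the PREVENA dressing set a floor on healing time in that arm. The point is weak: the wound is inspected on day 7, and with closure at 20 days or later, as assumed here, the floor never binds.

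Withdrawal is partly dealt with, because the Exclusion criteria remove patients who miss their clinic follow-up. Whether that rule is sound is a separate question.

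Three defences do not remove the problem. The qualifier at the end of the t-test sentence names no method that allows for censoring. The blinded photographs and visual analogue ratings are a separate outcome and do not feed the healing time. Nor is this a detail that an article leaves to a fuller document, since both the end of the interval and the test are stated.

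**Conclusion.** The point holds as a fault of definition and method. The recorded time ends at a contact that need not coincide with closure, and the t-test cannot treat an open wound as unresolved. That follows from the text alone and needs no assumption.

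The size and direction of any bias are conditional. On the assumed values, a true benefit of 3.75 days is recorded as about 1.3 days if home visits end early for half of SSI patients; the worst case is −1.2 days. The bias is nil if nurses always visit until closure, and runs the other way if infected wounds get extra visits after it. Only the 25% and 10% come from the protocol. The sums also assume that NPWT affects healing only through SSI and that early ending is equally common in both arms.

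The outcome is secondary and the primary SSI comparison is untouched. The change should be made, but the trial's main conclusion does not depend on it.

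**What to change.** - **Event:** the first date on which a nurse or investigator records complete wound closure, counted from the day of surgery.
- **Censoring:** a patient not recorded as healed is censored at the last wound assessment of any kind, at home, on referral or in clinic. Assessments at the study site must count; censoring at the last home visit alone could still remove infected patients early.
- **Analysis:** replace the t-test with Kaplan-Meier curves and a log-rank test or Cox model. Stratifying by the three randomisation strata is optional.

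The cost is one additional date per patient, obtained through the existing liaison with the nurses, and a different standard analysis. It requires no change to wound care or visit schedules. One limit remains: closure is seen only when someone looks, so the spacing of visits still limits the precision of the date.
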